***Secondary objectives***

We will assess, along with legal, health economic and ethical implications, whether the form:

Increases care for those documented as not for resuscitation, but for active treatment (defined as active treatment in the UFTO group, and no statement of ceiling of care in the DNACPR group). This will be measured by:

- 1. review by other specialities
  2. referral and acceptance to escalating care (e.g. HDU / ICU)
  3. radiological investigation
  4. prescription of “expensive” drugs (where “expensive” is from a predefined list supplied by pharmacy);

Specifically, we will assess whether introduction of the UFTO alters *in isolation and as a composite endpoint* the above mentioned factors.

- Alters length of stay or in-hospital mortality;
- Improves care towards the end of life by encouraging advance care planning;
- Reduces the number of patients who remain inappropriately for resuscitation as judged by total numbers;
- Improves understanding in all groups about the appropriate implications of the decision not to resuscitate, as assessed by qualitative interviews and questionnaires and ethnographic research;
- Creates a positive framework for discussions of treatment options with patients and their families, as assessed by qualitative interviews and questionnaires and ethnographic research;
- To map the current decision-making processes around resuscitation: both explicit and implicit factors, across all groups
- To assess all groups’ attitudes and feelings about the old DNACPR and new UFTO, and compare their differing perspectives
- To assess the ethical problems faced by professional staff in using the conventional DNACPR form and the new UFTO
- To establish what elements of experience from each differing perspective are felt to be associated with the question of resuscitation in order to recognise the ways it has meaning in terms of the overall expectations of care
- To learn from outcome data of the above to inform an optimised approach to resuscitation decisions framed by the UFTO.

Trial Design

EVALUATION OF THE UFTO

The form to be trialled has been developed as described in the introduction

Study Summary

A before and after study will be carried out on the respiratory and general medicine ward, and General Medical/endocrinology and elderly care ward (G4) at the West Suffolk Hospital. Patients under 18 or for palliative care only on admission or who have an admission of less the 24 hours will be excluded.

We will prospectively collect the previously described data for a 3 month period prior to introduction of the UFTO form. Education of clinical teams will then be carried out by members of the research team.

Following a “bedding in” period of a month the UFTO form will be introduced throughout the clinical area. During this period, we will administer questionnaires to consenting nurses, doctors, patients and relatives who have had a discussion about resuscitation. We will interview a representative sample of nurses, doctors and patients about their understanding of the UFTO, and their views on the education we provided.

Following introduction of the UFTO the quantitative and qualitative data set will be collected for up to a further 3 months, or as long as it takes to collect a sufficient sample size for statistical significance ( at least 108 patients not for resuscitation).

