**Secondary Outcomes**

The following will also be analysed and considered statistically significant at more stringent level 0.01 due to multiplicity of outcomes:

1. Assess whether introduction of the UFTO alters in isolation and as a composite endpoint frequency of referral to ICU,HDU,Medical Specialities, and out-of-hours medical care in those patients who have a not for attempted resuscitation instruction on their UFTO in comparison with those patients with conventional DNACPR forms, independent of MEWS scoring.

2. Assess whether the UFTO improves end of life care

3. Patient length of stay and in hospital mortality will also be examined

Recruitment rates will be monitored on an ongoing basis. No formal interim analyses are planned for this study. Confidence intervals and exact 2-sided p-values will be reported between group differences in outcomes and intention-to-treat analyses will be performed for whole group comparisons. The primary endpoint is restricted to the pre-defined subgroup of those with 'not for resuscitation' orders as described. Multivariate analyses using logistic regression for categorical endpoints, or multiple regression for continuous endpoints, will be used to develop suitable statistical models. Analyses will be carried out using SPSS software.

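### The care-intensity secondary outcome is specified twice, with conflicting populations and composites, and one version selects patients by a different rule in each group

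*Protocol*

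**What the plan says.** **Population.** Under Secondary objectives, the objective of increasing care applies to patients documented as not for resuscitation but for active treatment. That subset is "defined as active treatment in the UFTO group, and no statement of ceiling of care in the DNACPR group". Secondary Outcomes, item 1, compares referral "in those patients who have a not for attempted resuscitation instruction on their UFTO in comparison with those patients with conventional DNACPR forms", with no active-treatment condition and no ceiling-of-care rule. The Study Synopsis also frames the objective for those not for resuscitation, without restriction.

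**Composite.** The Secondary objectives list four measures: "review by other specialities", being referred and accepted for HDU or ICU care, "radiological investigation", and prescription of expensive drugs, where expensive "is from a predefined list supplied by pharmacy". These are to be examined "in isolation and as a composite endpoint". Secondary Outcomes, item 1, uses the same phrase for "frequency of referral to ICU,HDU,Medical Specialities, and out-of-hours medical care".

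**Context.** The Background says that DNACPR forms tell staff what to do at an arrest and are not meant to alter other care. It lists poor communication about the appropriate extent of treatment among the problems seen with them. The Trial Aims expect the UFTO to increase documentation of clear treatment plans.

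**The concern.** There are two linked problems.

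First, one outcome has two specifications. They share the wording about single and composite analysis, so they read as the same outcome, but they differ in who is analysed and in what counts as an event. Whoever runs the analysis could use either and describe it as planned.

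Second, the Secondary objectives version uses unequal entry rules. A UFTO patient enters on a positive record of active treatment. A DNACPR patient enters unless someone wrote down a ceiling. On the Protocol's own account, a DNACPR form does not address the extent of other treatment, so silence is weak evidence that active treatment was intended. The comparator may therefore keep patients with unwritten limits whose UFTO counterparts would be removed because the limit was recorded. The variable that decides entry is also one that the intervention is meant to change. If patients with limits are escalated less, part of any difference would reflect who was let in.

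**Working it through.** **Side by side**

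| Element | Secondary objectives | Secondary Outcomes, item 1 |
| --- | --- | --- |
| UFTO group | not for resuscitation, active treatment recorded | all with a not-for-resuscitation instruction |
| DNACPR group | DNACPR, no ceiling statement | all with a DNACPR form |
| Specialities | review | referral |
| HDU/ICU | referral and acceptance | referral |
| Radiology | in composite | absent |
| Expensive drugs | in composite | absent |
| Out-of-hours medical care | absent | in composite |

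The population differs, and no component matches in full: two overlap with different wording, two appear only in the first list and one only in the second. The Study Synopsis agrees with the right-hand column on population.

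**Possible size of the bias.** The Protocol gives no rates for this outcome, so there is no stated figure to reproduce, and every rate below is an assumption.

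Let pA and pL be the referral rates of patients intended for active and for limited treatment, the same in both periods (no true effect). Let w be the share of the DNACPR subset whose treatment was in fact limited. If the UFTO subset contains only patients intended for active treatment, then

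spurious difference (UFTO minus DNACPR) = pA − [(1 − w)pA + w·pL] = w(pA − pL).

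*Illustration.* Take 100 patients per period: 60 for active treatment with pA = 50%, and 40 limited with pL = 10%. The UFTO subset has 60 patients, 50% referred.

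- All ceilings written under DNACPR: w = 0, difference 0.
- Half written: subset 60 + 20 = 80; referred (30 + 2)/80 = 40%; difference +10 points. Check: w = 20/80 = 0.25 and 0.25 × 0.40 = 0.10.
- None written: subset 100; referred (30 + 4)/100 = 34%; difference +16 points. Check: 0.40 × 0.40 = 0.16.

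*Other assumed rates.*

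| pA, pL | w = 10% | w = 30% | w = 50% |
| --- | --- | --- | --- |
| 50%, 20% | +3 | +9 | +15 |
| 60%, 10% | +5 | +15 | +25 |

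The 0 to +16 range varies only the share of ceilings written. It is not an outer bound.

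**Chance of a false significant result.** This uses the 0.01 level that the Protocol sets for secondary outcomes and a two-sided Fisher's exact test (named in the Protocol for the primary endpoint and assumed here).

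- With 108 patients in each subset, an upper-end assumption because 108 is the target for all patients not for resuscitation: 1.4%, 9.0% and 32.5% along the first row of the table; 2.6%, 32.6% and 85.4% along the second. With no misclassification (50% in both groups) it is 0.8%.
- With the illustration scaled to 108 patients not for resuscitation per period: 65 v 86 patients (50% v 40%) gives about 8%; 65 v 108 (50% v 34%) gives about 28%; 65 v 65 (50% in both) gives about 0.6%.

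The stricter threshold limits chance findings. It does not protect against a systematic difference in who is included.

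**The case against.** **The direction is not certain.** A reader might infer that the definition necessarily favours the UFTO. The documents do not support that, because the form is a supplement that is not shown. If active treatment were recorded by default, a share v of the UFTO subset would also be limited patients. The difference would then be (w − v)(pA − pL), which is zero when v = w and negative when v exceeds w. This stands: the direction is probable, not established.

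**Lower referral without a ceiling may be the effect under study.** A reader might also treat every unescalated DNACPR patient without a ceiling as a selection artefact. But if a DNACPR order is not meant to alter other care, a patient with no stated ceiling is formally for active treatment, and unjustified non-escalation of such patients is the inequality that the trial wants to remove. This stands in part. The difference would mix that effect with unwritten but considered limits, and the definition cannot separate them.

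**The size is assumed.** No document figure supports the rates used. Patients for palliative care only on admission are excluded from both groups, which may remove some of those escalated least. This stands.

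**The all-patient comparison is not free of the problem.** The UFTO is completed for every patient and is expected to leave fewer inappropriately for resuscitation, so who carries a not-for-resuscitation decision may change between periods. A notes-based rule for active treatment would also depend on documentation that the UFTO is meant to change. Both points stand as limitations of the remedy.

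None of this answers the contradiction between the two sections.

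**Conclusion.** The contradiction is certain on the face of the Protocol: one care-intensity outcome, two populations and two composites, unreconciled.

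The unequal entry rule is a real but unquantified risk of bias. It probably favours the UFTO, on two conditions that the documents do not settle: that UFTO entries are made deliberately, and that patients with unwritten limits are escalated less. Under the main set of assumed rates the spurious difference is 0 to about +16 points, and other plausible inputs give more or less. It would be wrong to conclude that an observed difference must be an artefact.

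The reach is limited to this secondary outcome. Neither the MEWS primary endpoint nor the later Global Trigger Tool endpoint uses the active-treatment definition. The point should be corrected, but it does not undermine the main comparison.

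**What to change.** 1. **Population.** Make the comparison of all patients not for resuscitation, already stated in the Study Synopsis and Secondary Outcomes, the planned analysis of this outcome in both periods, and align the Secondary objectives with it.
2. **Composite.** State one list in both sections and report the remaining components singly. The Secondary Outcomes list is a natural candidate because it already sits with that population and the 0.01 level, but what matters is that there is one list. Say also whether the speciality component is review or referral, and whether HDU/ICU acceptance counts.
3. **Active-treatment subset.** If kept, label it exploratory, apply the same criterion in both periods, and note that documentation itself is expected to change under the UFTO.

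**Cost.** Items 1 and 2 are mainly wording. Data Collection already covers form details, ICU/HDU, speciality and out-of-hours referral, radiology and expensive drugs; it names ICU/HDU referral but not acceptance. Item 3 would mean reclassifying patients from the notes.

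**Downsides to state.** The all-patient comparison answers a slightly broader question than the Secondary objectives ask, and it remains open to a change in who receives a not-for-resuscitation decision. The amendment on the new dataset records that an initial analysis has been done, so a choice of population or composite made after it must be declared post hoc.

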**Number of Subjects**

Two clinical areas will be trialed: A respiratory and general medical ward and a care of the elderly/diabetes and endocrinology ward. The two wards combined have an average of 8 admissions a day, which should allow us to obtain the 108 patients not for resuscitation admissions necessary, estimating that one fifth of patients have a decision not to attempt resuscitation. We are powered to 108 patients in the subgroup of interest; it is possible that the overall sample sizes will be larger or smaller depending on rate of decisions about resuscitation. Staff and relatives will also be involved in the research, taking part in interviews, questionnaires, and ethnographic research.

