**Study duration**

Patients will be involved in the study until their discharge or transfer to another ward. The end of the trial will occur when we have 108 patients who are not for resuscitation in each group (estimated at 720 patients total in each group, total sample size 1440).

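### A secondary objective is judged by raw totals although the two periods may differ in length and admissions, so the total is confounded by period length

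*Protocol*

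**What the plan says.** Under Secondary objectives, the protocol will assess whether the form "Reduces the number of patients who remain inappropriately for resuscitation as judged by total numbers". The synopsis lists the same objective without any measure. The Secondary Outcomes list under Quantitative Analysis neither includes this outcome nor restates it as a proportion.

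Period length and size are set in three places:

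- **Study Summary, before period:** "We will prospectively collect the previously described data for a 3 month period prior to introduction of the UFTO form".
- **Study Summary, after period:** collection runs for "up to a further 3 months, or as long as it takes to collect a sufficient sample size for statistical significance", with at least 108 not-for-resuscitation patients as the target.
- **Study duration:** "The end of the trial will occur when we have 108 patients who are not for resuscitation in each group". About 720 patients per group are expected, as an estimate.
- **Number of Subjects:** "The two wards combined have an average of 8 admissions a day", "estimating that one fifth of patients have a decision not to attempt resuscitation", and "it is possible that the overall sample sizes will be larger or smaller depending on rate of decisions about resuscitation".

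The Trial Aims give a related hypothesis as a percentage: patients who die in hospital without clear guidance on resuscitation should fall from near 20% to near zero.

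**The concern.** A total can be compared between two periods only if both contain about the same number of eligible admissions. Nothing in the protocol secures this. The before period ends on a date. The after period may end on a count, and how soon that count is reached depends on the share of patients given a not-for-resuscitation decision, which the form may itself change. The total could then rise or fall with no change in practice, or exaggerate a real change.

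There is also a second, separate gap. A total of patients still for resuscitation does not distinguish those for whom that status was inappropriate.

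**Working it through.** **Inputs.** Admissions are 8 a day and the share not for resuscitation is s = 1/5 (Number of Subjects). The count is 108 (Study duration, Sample size determination). Three months is taken as 90 days, which is an assumption. The exclusions (under 18, stays under 24 hours, palliative care only on admission) are ignored because the protocol gives no figures for them.

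**The plan's own figures.** 8 × 90 = 720, which matches the expected size per group. The count of 108 is also reproducible: for 60% versus 40% (assumed, as the base rate is not stated), exact power of Fisher's test at 108 per group is 80.2%. However, 108 out of 720 implies s = 15%, whereas one fifth of 720 is 144. At the stated one fifth, the count would be reached before 3 months are over.

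**Formulas.**

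- Calendar-based period: admissions = 8 × 90 = 720; for resuscitation = 720 × (1 − s).
- Count-based period: admissions = 108/s; days = 108/(8s); for resuscitation = 108 × (1 − s)/s.

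At s = 20% the count-based period has 108/0.20 = 540 admissions in 540/8 = 67.5 days, of which 540 × 0.80 = 432 are for resuscitation. The 90-day period has 720 × 0.80 = 576. The ratio is 432/576 = 0.75.

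**Cases.** Shares other than 20% are illustrative, except 15%, which is implied by 108/720.

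| Share before, after | Before period ends | After period ends | Total for resuscitation | Change in total | Proportion for resuscitation |
|---|---|---|---|---|---|
| 20%, 20% | 90 days | at 108 (67.5 days) | 576 to 432 | −25% | 80% to 80% |
| 10%, 10% | 90 days | at 108 (135 days) | 648 to 972 | +50% | 90% to 90% |
| 15%, 15% | 90 days | at 108 (90 days) | 612 to 612 | 0 | 85% to 85% |
| 20%, 20% | at 108 | at 108 | 432 to 432 | 0 | 80% to 80% |
| 20%, 25% | 90 days | 90 days | 576 to 540 | −6.25% | 80% to 75% |
| 20%, 25% | 90 days | at 108 (54 days) | 576 to 324 | −43.75% | 80% to 75% |
| 20%, 25% | at 108 | at 108 | 432 to 324 | −25% | 80% to 75% |

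The last three rows have the same change in practice. The relative fall in the proportion is 1 − 75/80 = 6.25%. The total shows 6.25%, 43.75% or 25%, depending only on how the periods end. Applying the count rule to both periods removes the distortion when the share is constant, but not when it changes.

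**Those inappropriately for resuscitation.** The table counts everyone for resuscitation. If an assumed 10% of admissions were inappropriately so in both periods, the 20% case gives 720 × 0.10 = 72 before and 540 × 0.10 = 54 after. This is again a 25% fall, at an unchanged 10%.

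**The case against.** The strongest reply is that the protocol uses the word number loosely. The Trial Aims speak of a number falling and then give percentages. The MEWS-based primary endpoint is called a number of patients, yet it is powered as a proportion with Fisher's exact test. The Quantitative Analysis section plans intention-to-treat whole-group comparisons and logistic regression for categorical endpoints, which use per-patient denominators. No test on raw totals is specified, and a statistical analysis plan may settle the measure.

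This makes it plausible that a proportion was intended. It does not cancel the wording, because here the protocol goes beyond a loose noun and names totals as the basis of judgement. No later section corrects it.

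Three further points stand and limit the finding:

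- The 25% figure is one scenario. The Study Summary sets 108 as a minimum, so collection may continue past it. If both periods have equal admissions, there is no distortion.
- A reader might infer that the total reflects period length and not the form at all. The documents do not support that. A total equals admissions times rate, so any effect of the form is still in it, mixed with exposure.
- A reader might also infer that moving to a proportion would capture inappropriateness. It would not: the proportion remaining for resuscitation is as silent on that as the total.

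**Conclusion.** The point holds as one of confounding. Judged by totals, this secondary objective cannot separate a change in practice from a difference in period length, because the protocol lets length and admissions differ and allows an end point that depends on the rate under study. On the protocol's own 8 admissions a day and one fifth not for resuscitation, the apparent fall with no effect is 25% (576 to 432). This assumes 90 days before, an after period stopped at exactly 108, and no exclusions. It would be zero with equal admissions, and an increase if the share were below 15%.

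The point is confined to a secondary objective. It touches neither the MEWS-based primary endpoint, which was powered as a proportion, nor the amended one, which is a rate per 1000 bed days. It should be corrected, but it does not threaten the main comparison.

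**What to change.** In Secondary objectives, replace the reference to totals with the proportion of eligible admissions that remain for resuscitation in each period, reported with numerator, denominator and a Newcombe 95% confidence interval for the difference. The amendment's Statistical Analysis section already uses that method for differences in proportions. Add the outcome, so defined, to the Secondary Outcomes list.

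Because this proportion does not measure inappropriateness, also report the percentage of in-hospital deaths without a documented resuscitation decision, which is close to the quantity in the Trial Aims hypothesis. State its limitation alongside: the new form is meant to be completed for every patient, so this percentage may approach zero through form completion alone.

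The cost is wording and a short reanalysis. Data Collection already records form completion with its date, and discharge or death. Logistics of Data collection cross-checks against the full list of ward admissions, so the denominators exist. Since the amendment reports that an initial analysis has been done, the change should be dated and described as made after it.

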**Education Package**

“Education of teams” will consist of a standardised presentation about using the UFTO, posters for clinical areas and information leaflets for staff (tailored for nurses and doctors to read after the education session. Members of the study team will answer any further questions in person or by email after the education period. A mini site within the hospital intranet will be created to support individuals using the new form.

